#### Community ART distribution model by healthcare worker (6-month supply of drug)

Participants enrolled at facilities in this arm will be given a 6 months’ supply of their ARVs at study enrolment. Their next ART refill will be conducted in 6 months in the community at a health outreach or health post (halls, churches or kiosks). These encounters in the community will be on an individual provider-patient basis, not as part of a CAG. The ART refill will be conducted by a healthcare worker who has been appropriately trained and certified for dispensing ART to stable patients. Study participants’ adherence will be assessed at this community distribution point as well as screening for TB, pregnancy, and other common conditions. Patients found to have any conditions that cannot be managed in the community will be referred to the health facility for further follow-up. These participants will continue to receive 6 month refills in the community if they remain stable (i.e. have VL less than 1000 copies per mL). Stable participants will be required to have a clinical consultation and VL done at the facility at 12 months and 24 months after enrolment.

Co-trimoxazole (CPT) and isoniazid (IPT) will also be provided to all arms based on the assigned ART dispensing interval and Lesotho guidelines.

### Study measures and outcomes (data collection matrix)

The schedule of visits and evaluations to be done are outlined see Additional file 1. The primary outcomes to be compared between arms for this study are retention and VL suppression. Secondary outcomes will include the following (i) comparisons in cost effectiveness between arms, (ii) acceptability of models to patients and service providers and (iii) measurable gains in decongestion in facilities through motion time assessments/analysis.

### Entry visit/baseline procedures

For those that enrol, the following detailed data will be collected and recorded from clinical and medical record review: HIV history, HIV-related medications, date of ART initiation, prior adherence/VL data, socio-demographic data including age, gender, level of education, estimated distance and time to travel to clinic, employment status, disclosure status and marital status. Costing data (patient cost data) including travel costs to clinic, opportunity cost of time spent on medication pickup visits etc., will be recorded.

### Viral load testing for enrolled patients (at 12 and 24 months)

As the study will be using VL results from routine monitoring as an inclusion criterion, some participants will have a VL test due soon after enrolment into the study. To synchronize patient care and study VL tests, due routine VL tests will be done as scheduled unless the test is due at 2 months before or after the required study-specific VL test at 12 and 24 months for the study, in which case the study-specific VL will be used for patient management. At 12 and 24 months after enrolment in the study, all patients are required to visit the facility for a VL test.

In this study, there will be no active contact with study participants during the period of follow-up. However, when participants are due for the above-mentioned routine, annual VL assessments, study staff will help ensure each site has capacity to collect these samples and will support systems that help to provide results back to sites. VLs will only be performed on individuals who return for visits and no tracing will be performed by the study for obtaining annual VLs. VLs will be considered within the window for the annual visit if they are performed in a window of +/− 90 days.

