### Study intervention: differentiated models of care for MMD of ART

#### Three month dispensing model at health facilities

Providers at facilities randomized to three-month dispensing will be expected to provide all enrolled patients with a 3-month supply of ART. All other aspects of care will be as standard of care for the enrolling clinic, though routine clinic visits will occur every 90 days instead of the standard of care interval. Information about ideal storage conditions for ART will be provided by the clinic.

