#### Community ART group (CAG) model (3-month supply of drug)

Study participants enrolled at facilities in this arm will join new or previously existing CAGs or will already be members of a CAG. Their first 3-month supply of drugs will be at enrolment facility, whilst the next ART refills will be through CAGs. The CAG will consist of 4–12 participants, who live in a similar geographic location and who all attend the same health care facility. The members’ appointments will be synchronized to ensure their scheduled clinic visits will be on the same day. The CAG will nominate a CAG leader and will meet on a 3-monthly basis in the community at a venue of their choice to access treatment. Stable study participants will be required to have a clinical consultation and VL testing at the facility at 12 and 24 months after enrolment in the study. Each member of the CAG will collect their own 3-month supply of ART from the clinic on this day. Participants who become ill at any stage of the study will report to the clinic as soon as possible. A CAG representative will distribute the drugs to the other CAGs members at the CAG meeting on the same day or the following day. The dates of these visits need to be noted by the facility so that all drugs are pre-dispensed and ready at this visit date.

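### The ±90-day viral load window spans two scheduled facility visits in the control arm but one in each community arm, so the chance of obtaining a countable viral load is unequal

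*Protocol article*

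**What the plan says.** The section on viral load testing at 12 and 24 months sets one window for all arms: "VLs will be considered within the window for the annual visit if they are performed in a window of +/− 90 days". It also ties measurement to attendance: "VLs will only be performed on individuals who return for visits and no tracing will be performed by the study for obtaining annual VLs". Every participant is due a facility VL at 12 and 24 months, whatever the arm.

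The arms differ in how often they bring a patient to the facility:

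- **Control (3MF):** "routine clinic visits will occur every 90 days instead of the standard of care interval" (three-month dispensing model).
- **3MC:** participants are "required to have a clinical consultation and VL testing at the facility at 12 and 24 months after enrolment". At the refills in between, "A CAG representative will distribute the drugs to the other CAGs members at the CAG meeting" (CAG model).
- **6MCD:** "Stable participants will be required to have a clinical consultation and VL done at the facility at 12 months and 24 months after enrolment". Refills take place elsewhere: "Their next ART refill will be conducted in 6 months in the community at a health outreach or health post" (community distribution model).

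The Discussion expects some VL results to be missing. VL suppression is listed as a primary outcome under the study measures and appears in primary objective (i), although the Discussion calls it secondary. The costing section also has an outcome based on patients who are both retained and suppressed.

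**The concern.** A window that is the same on paper need not give the same chance of measurement. Here its half-width equals the visit interval of one randomised arm. If a control patient's VL is not drawn at month 12, the next routine clinic visit can still fall inside the window. A 3MC or 6MCD patient has no second scheduled facility visit there, and nobody traces them. The number of scheduled chances to be measured therefore depends on the allocated arm.

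At stake are the between-arm VL comparisons and the combined retained-and-suppressed cost outcome. If a missing VL is counted as not suppressed, the community arms lose ground because of their visit calendar. If only observed VLs are analysed, the arms are compared on differently selected patients. The comparison of 6MCD with 3MC is not affected, because both have one scheduled facility visit in the window.

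**Working it through.** The plan gives no figure for VL completeness, so there is none to reproduce. Its sample size concerns 12-month retention and does not enter this point.

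**Step 1. Count scheduled facility visits in the window.** Inputs are the ±90-day window, the 90-day control interval and the 12- and 24-month facility visits of the community arms. The document does not fix the length of a year in days, so three readings are shown.

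| Reading | 12-month window | Control visits inside | 3MC / 6MCD |
|---|---|---|---|
| 90-day visits, 365-day year | 365 ± 90 = days 275–455 | 360, 450 (two) | one |
| 90-day visits, 360-day year | 360 ± 90 = days 270–450 | 270, 360, 450 (three, two on the boundary) | one |
| Calendar quarters, 365 / 4 = 91.25 days | days 275–455 | 365 (one) | one |

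At 24 months with a 365-day year the window is 730 ± 90 = days 640–820. It holds control visits at days 720 and 810, against one in each community arm.

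The third reading gives equality only just. The neighbouring control visits fall at 365 − 91.25 = 273.75 and 365 + 91.25 = 456.25, each 1.25 days outside.

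**Step 2. Completeness.** Assumptions, not in the documents: a visit yields a usable VL with probability p, and a VL missed at the annual visit is retried at the next control visit, inside the window, with probability q. Then

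- community completeness = p
- control completeness = p + (1 − p)·q·p
- gap = p(1 − p)q

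| p | q = 0 | q = 0.25 | q = 0.5 | q = 1 |
|---|---|---|---|---|
| 0.7 | 0 | 5.2 | 10.5 | 21.0 |
| 0.8 | 0 | 4.0 | 8.0 | 16.0 |
| 0.9 | 0 | 2.2 | 4.5 | 9.0 |

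(percentage points, control minus community)

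**Step 3. Suppression.** Assume that 95% of patients are truly suppressed in every arm and q = 1, the extreme case.

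- *Missing counted as not suppressed.* The apparent difference is 0.95 × gap: 0.95 × 16.0 = 15.2 points for p = 0.8, and 0.95 × 9.0 = 8.6 points for p = 0.9, both in favour of control.
- *Observed VLs only, late-tested patients equally suppressed.* The difference is 0.
- *Observed VLs only, late-tested patients 85% suppressed.* For p = 0.8, control shows (0.80 × 0.95 + 0.16 × 0.85) / 0.96 = 0.896 / 0.96 = 93.3%, against 95.0% in the community arms. That is 1.7 points against control. For p = 0.9 it is 0.9 points against control.

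The direction therefore changes with the handling of missing VLs.

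**Step 4. Check a narrower window.** ±45 days gives 365 ± 45 = days 320–410 and 730 ± 45 = days 685–775. Control visits at days 360 and 720 are inside; those at 270, 450, 630 and 810 are outside. Calendar-quarter visits at days 365 and 730 are also the only ones inside. Each arm then has one scheduled facility visit per window.

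**The case against.** The scheduled test is the same in all arms, one VL at 12 months and one at 24. The second control visit is only an opportunity: no passage says that a missed VL is redrawn there, and q could be zero. On the literal schedule that visit lies only five days inside the window (450 against 455), so a late attender falls outside. With exact calendar quarters the count is one against one. Community patients who attend the facility late, within 90 days, also count, and a CAG representative may be at the clinic more often. All of this stands. It limits the size of the effect but leaves the unequal scheduled opportunity in place. The calendar-quarter reading does little to rescue the window, since a visit just over a day early or late brings a second control visit inside.

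A further defence is that any bias favouring control works against a non-inferiority claim and so is conservative. That is true only if missing counts as not suppressed. With observed VLs only, and late-tested patients less often suppressed, control looks worse and non-inferiority becomes easier to claim.

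The wide window also has merit. It matches the 90-day rule for loss to follow-up, so under ±45 days a patient who returns 46 to 90 days late would be retained yet have no countable VL. CAG appointments are synchronised by group, so a member's annual visit may not fall on that member's own date. These points argue against replacing the ±90-day window outright.

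**Conclusion.** The point holds as one of unequal opportunity for VL ascertainment. On the stated 90-day interval and a 365-day year, control has two scheduled facility visits per window and each community arm has one, at both 12 and 24 months. Completeness may favour control by p(1 − p)q, which for p = 0.8 is anywhere from 0 to 16 points. Both p and q are assumed, and the documents do not fix the size.

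A reader might infer more: that suppression is measured more favourably in control, by 9 points or more, and that this exceeds the 3.25% non-inferiority limit. The documents do not support that. The direction for suppression needs a rule for missing VLs, which this article does not give and which may stand in an analysis plan not shown. Gaps of that order (9 points at p = 0.9, 21 at p = 0.7) require every missed control VL to be retried, so they are the upper end of this model. The 3.25% limit was set for retention and is not a benchmark for VL completeness or suppression.

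**What to change.** For the between-arm VL comparisons and the retained-and-suppressed outcome:

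- Prespecify, alongside the ±90-day analysis, one whose window holds one scheduled facility visit in every arm. An example is the VL nearest to month 12 or 24 within ±45 days, one result per participant.
- Report VL completeness by arm for both windows.
- Require the VL conclusion to be consistent across the two before it is claimed.

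The ±90-day analysis stays, for the reasons given in its defence. The cost is one extra analysis and some wording. The narrower analysis will contain fewer late VLs in all arms, including community visits moved by group scheduling. Patient visits and VL testing do not change.

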### Study end points and definitions

Endpoints will be determined by record reviewing. The primary endpoint will be reached (12 months) and re-assessed after the 24-months. Endpoint data collection will include:(i)Retention in care defined as participant attrition, where attrition is defined as either death (all-cause) or loss to follow-up (LTFU). LTFU will be defined as no facility or ART collection for > 90 days after the last missed scheduled ART collection. Participants with documented transfers to another clinic will be considered retained at the next immediate time point (12 or 24 months), and will then be censored.(ii)Suppressed VL of < 1000 copies/mL done as part of annual VL or performed at any other time during the follow-up, if ordered by clinician due to clinical concern (secondary).

The following will be considered not retained unless otherwise noted:(i)Retained in care but with transitioned off assigned study arm for any reason (patient preference, provider preference, development of ART toxicity requiring switch and closer monitoring and any other complications)(ii)Transferred to another clinic (if a documented transfer, will be considered retained and analysed as such at the next assessment point.(iii)Death.

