### Management of patients who develop comorbidities and those that become pregnant

Participants who develop TB, other opportunistic infections or comorbidities may require more frequent follow-ups than required by their dispensing interval. If they are in the 3MC or 6MCD arm, they will be considered unstable and are to be followed up at the facility hence transitioned off the study arm. These individuals will remain in observational follow-up but considered not retained for analyses. Providers will make these decisions and the study will track such outcomes. Frequency of ART dispensing will be determined based on national guidelines and clinician assessment. These events will be captured through patient routine records. Women who become pregnant whilst in the study will also require more frequent clinical visits for antenatal and postpartum care than required by their dispensing interval. If they are in the 3MC or 6MCD arm, they will return to be followed up at the facility. Frequency of ART dispensing will be determined based on national guidelines for ART in pregnancy and clinician assessment. These events will be captured through patient routine records. These individuals will remain in observational follow-up.

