#### Statistical analysis, power and sample size considerations

Descriptive data of the study population stratified by treatment arm will presented as medians and interquartile ranges for continuous variables and proportions for categorical variables.

Our analysis will use an intention-to-treat approach in which generalized estimating equations (GEE) will be computed to estimate risk differences and risk ratios and associated 95% confidence interval for the effect of each intervention arm compared to the control (Patients receiving 3 monthly ART supply at facilities), specifying for clustering by facility. A small cluster size variance correction will be used. Should we identify any baseline imbalances between study arms, we will adjust for these through multivariable regression models and report adjusted effect measures and corresponding 95% confidence intervals.

Qualitative analysis will be employed in this study to ascertain feasibility, acceptability of CAGs and community ART distributions by patients and service providers. Summative content analysis which involves counting and comparisons of keywords or content, followed by the interpretation of the underlying context will be conducted. The data will be further analysed for emerging key themes and the findings will be interpreted based on each research question. Quotes will also be extracted for each of the themes that emerge from the data. It is anticipated that MMD will reduce both facility and patient costs of treatment and that it will be cost-saving compared to standard of care. For facilities, fewer clinic visits by patients should save the time of providers and support staff. For patients, fewer clinic visits are expected to reduce the costs of travel and to save time. The study will estimate differences in both provider and patient costs. Cost-effectiveness will be estimated as the average cost per successful outcome (patient retained at 12 and 24 months).

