### Sample size estimate

Sample sizes were determined for a cluster randomized non-inferiority trial with retention in care at 12 months as the primary outcome. A total of 30 study sites will be available for randomization, with three study arms, 10 clusters per arm, and participant enrolment numbers will be assumed to be equal at each site. The probability of patient attrition 12 months after study enrolment is assumed to be 5%. An intra-cluster correlation coefficient of 0.01 for patient retention/attrition amongst stable ART patients is assumed from a previous cluster randomized trial including stable ART patients [9]. The non-inferiority limit is specified as 3.25%. Assuming α = 0.05, power of 85%, and using a one-sided Z-test (un-pooled) statistic, approximately 192 enrolled participants per facility will be required with a total sample size of 5760 participants, representing 1920 participants per arm.

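### Retention is defined in two incompatible ways, and the illness-triggered not-retained coding is written only for the community arms, which tilts both comparisons with 3MF toward failing non-inferiority

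*Protocol article*

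**What the plan says.** All references are to the protocol article.

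- **Study end points and definitions.** The section first states that "attrition is defined as either death (all-cause) or loss to follow-up (LTFU"). It then lists categories that count as not retained, the first being "Retained in care but with transitioned off assigned study arm for any reason". The reasons given there include patient or provider preference, toxicity and other complications, and no arm is exempted.
- **Management of patients who develop comorbidities and those that become pregnant.** For TB, other opportunistic infections or comorbidities: "If they are in the 3MC or 6MCD arm, they will be considered unstable and are to be followed up at the facility", which the article treats as leaving the study arm. Their analysis status is explicit: "These individuals will remain in observational follow-up but considered not retained for analyses". Nothing equivalent is written for 3MF. Pregnant women in 3MC or 6MCD also return to the facility, but the not-retained coding is not repeated for them.
- **Community ART distribution model (6MCD).** Community refills continue "if they remain stable (i.e. have VL less than 1000 copies per mL"). The article does not say how a patient who loses this status is scored for retention.
- **Sample size estimate.** "The probability of patient attrition 12 months after study enrolment is assumed to be 5" per cent. No allowance for transitions and no difference between arms is stated.

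**The concern.** The first definition measures whether a patient is alive and in care. The second measures whether the patient is still on the assigned delivery model. The primary objectives are worded as non-inferior retention in care, which matches the first.

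The second definition is also unlikely to act equally across arms. A 3MC or 6MCD patient who develops TB and returns to the facility is scored as a failure while still receiving care. A 3MF patient with the same illness is already followed at the facility and need not count as having left the arm. Two community-arm groups have no clear status: women who become pregnant, and 6MCD patients who lose the viral-load condition. They become failures only through the any-reason clause.

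At stake is a false failure of non-inferiority. A community arm with exactly the same death and loss to follow-up as control could miss the margin because of a coding rule.

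**Working it through.** **Inputs from Sample size estimate.** Attrition 5%; margin 3.25 points; ICC 0.01; 10 clusters per arm; 192 patients per cluster; 1920 per arm. The test is given as: "Assuming α = 0.05, power of 85%, and using a one-sided Z-test (un-pooled) statistic".

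**Input not in the article.** The share of patients moved off the assigned model by 12 months. This is an assumption, shown as a range. Transitions are added to the 5% with death or loss to follow-up.

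**Step 1. Reproduce the plan.**
- Design effect = 1 + (192 − 1) × 0.01 = 2.91. Effective size per arm = 1920 / 2.91 = 659.8.
- SE = sqrt{[pC(1 − pC) + pT(1 − pT)] / 659.8}
- Power = Φ[(0.0325 − (pT − pC)) / SE − 1.645]
- With pC = pT = 0.05: SE = sqrt(0.0950 / 659.8) = 0.0120. Power = Φ(2.708 − 1.645) = 85.6%, against the stated 85%.
- Solving for sample size gives 647 effective patients per arm; 647 × 2.91 = 1883, against the stated 1920.

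The stated figure therefore rests on equal not-retained risk in the two arms compared.

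**Step 2. Transitions in the community arm only (pC = 0.05).**

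| Excess (points) | pT | SE | Power |
|---|---|---|---|
| 0 | 0.050 | 0.0120 | 85.6% |
| 0.5 | 0.055 | 0.0123 | 72% |
| 1 | 0.060 | 0.0125 | 56% |
| 2 | 0.070 | 0.0131 | 25% |
| 3.25 | 0.0825 | – | 5% |

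In the last row the excess equals the margin, so the numerator is zero and power is Φ(−1.645) = 5%.

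**Step 3. Transitions in both arms.** With 2% in the community arm and 1% in control, pT = 0.07 and pC = 0.06. SE = sqrt[(0.0651 + 0.0564) / 659.8] = 0.01357. Power = Φ(0.0225 / 0.01357 − 1.645) = Φ(0.013) = 51%. The net excess drives the loss. Equal transitions cost less, through variance alone: 80.0% if 1 point is added to every arm and 74.8% if 2 points are.

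**Step 4. Can enrolment compensate?** At a 1-point net excess with no control transitions, 85% power needs (1.645 + 1.036)² × (0.0475 + 0.0564) / 0.0225² ≈ 1476 effective patients per arm. With 10 clusters and ICC 0.01, effective size cannot exceed 10 / 0.01 = 1000 however many patients each facility enrols.

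**The case against.** Several points on the other side are sound and limit what can be claimed.

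- **The any-reason clause covers every arm.** 3MF is itself a fixed model with 90-day visits, so a control patient moved to closer monitoring could also be scored as off-arm. A reader might infer that control patients with the same event always stay retained; the text does not settle that. Only the net excess biases the contrast, so the control-zero rows are the unfavourable end of the range.
- **Intention-to-treat.** A reader might see a conflict with "Our analysis will use an intention-to-treat approach". There is none. Intention-to-treat fixes the arm in which a patient is analysed, and scoring a transition as failure in that arm is a composite endpoint compatible with it. Equally, analysis by assigned arm does not remove an imbalance built into the outcome.
- **Viral load.** A reader might infer that virologic failure simply becomes retention failure in 6MCD. The article does not say so; it follows only by joining the refill condition to the any-reason clause. Study viral loads are taken at 12 months, within 90 days either side, so many such moves would fall at or after the 12-month assessment. Earlier routine tests leave a smaller contribution.
- **Direction.** The error runs against the community arms and does not raise the chance of a false non-inferiority claim. A true benefit could offset it: with death and loss to follow-up 1 point lower in a community arm, 2% transitions there and none in control leave a net excess of 1 point, and power is 56% instead of 25%.

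What remains is the contradiction in the endpoint definition and a coding rule whose illness trigger is written for two arms out of three.

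**Conclusion.** The point stands. The primary endpoint has two incompatible definitions. Followed as written, the illness-triggered coding biases 3MC versus 3MF and 6MCD versus 3MF toward falsely failing non-inferiority. 6MCD versus 3MC shares the same illness and pregnancy moves and is largely unaffected.

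The direction comes from the text; the size does not. A reader might conclude that the trial has lost its stated power, but the article gives no transition rate and supports no such unconditional statement. The power figures assume equal 5% death or loss to follow-up, ICC 0.01 and one-sided alpha 0.05. They show that a net excess of only 1 point is enough to bring power down to between one half and 56%. This should be resolved before the 12-month analysis because it sits in the primary endpoint and can change the conclusion.

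**What to change.** Reconcile the endpoint section, the comorbidity and pregnancy section and the sample size section as follows.

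1. Make death or loss to follow-up the 12-month primary retention endpoint, applied identically in all three arms whatever dispensing model the patient is then on.
2. Remove the not-retained coding of transitions from the endpoint and comorbidity sections. This changes scoring only; patient care is untouched.
3. Report transition off the assigned model, by arm, as a separate implementation outcome.
4. Keep the on-model composite as a sensitivity analysis, counting the same recorded trigger events in all three arms, with pregnancy and loss of viral suppression explicitly assigned. In the community arms the move is a provider decision, so the matching in 3MF should use recorded events.
5. State that follow-up continues after every kind of transition. It is documented for comorbidity and pregnancy, but not for moves due to preference or toxicity.

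The cost is revised wording, one by-arm table and one sensitivity analysis. The planned sample size then matches its 5% assumption.

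There is a real downside. Patients who return to facility care count as retained, which can draw the arms together and favour non-inferiority. The by-arm transition rates and the composite must therefore stand beside the primary result. The sensitivity analysis does not itself measure that dilution.

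If the team does intend the on-model composite as primary, it should say so and re-power with arm-specific transition rates.
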